## Abstract

**Background:**

HIV-related stigma negatively impacts HIV prevention, treatment, and care, particularly among children and adolescents in sub-Saharan Africa. Interventions that are culturally grounded and relevant for addressing root causes may reduce the stigma experienced by HIV-positive and HIV-affected young people. This study, to be conducted in a post-conflict, rural setting in Omoro District, Uganda, will develop and evaluate a transformative  arts-based HIV-related stigma intervention rooted in local cultural knowledge to reduce stigma and improve HIV prevention and care for young people living with HIV. The intervention will be delivered to young people attending school by community Elders, with the support of teachers, through the transfer of local cultural knowledge and practices with the aim of re-establishing the important cultural and social role of Elders within a community that has suffered the loss of intergenerational transfer of cultural knowledge throughout a 25-year civil war.

**Methods:**

A formative research phase consisting of interviews with students, teachers, and Elders will inform the intervention and provide data for study objectives. Workshops will be delivered to Elders and teachers in participating schools to build capacity for arts-based, educational workshops to be conducted with students in the classroom. The intervention will be evaluated using a stepped-wedge cluster-randomized trial. Government-funded schools in Omoro District will be randomized into three blocks, each comprised of two primary and two secondary schools (*n*=1800 students). Schools will be randomly assigned to a crossover sequence from control to intervention condition in 8-week intervals. A process evaluation will be implemented throughout the study to evaluate pathways between intervention development, implementation, and effects.

**Discussion:**

This study will generate comprehensive, in-depth participatory research and evaluation data to inform an effective and sustainable protocol for implementing arts-based HIV stigma interventions for young people in school settings. Findings will have widespread implications in post-conflict settings for HIV prevention, treatment, and care.

**Trial registration:**

ClinicalTrials.gov NCT04946071. Registered on 30 June 2021.

**Supplementary Information:**

The online version contains supplementary material available at 10.1186/s13063-022-06643-9.

## Background

Children and adolescents growing up with HIV infection or those living with parents or caregivers who live with HIV or AIDS experience various forms of stigma. Stigma refers to attitudes and beliefs that lead people to reject, avoid, or fear those they perceive as different and can lead to mistreatment and reduced access to power and opportunities [1]. HIV-related stigma continues to negatively impact HIV prevention, treatment, and care. For instance, HIV-related stigma has been associated with reduced uptake of voluntary counseling and testing [2], reduced likelihood of HIV status disclosure [3], and poses a significant barrier to antiretroviral therapy (ART) medication adherence, contributing to high rates of HIV mortality, especially in sub-Saharan Africa [4, 5]. Additionally, HIV stigma contributes to mental health issues in children and adolescents, such as anxiety and depression [6]. It may lead to school drop-out due to bullying, discrimination by peers and teachers and suicidal ideation [7]. As a result, young people face the dual burden of physical illness from living with the HIV virus and psychosocial distress resulting from stigma and discrimination.

Despite the importance of addressing HIV-related stigma and discrimination among young people, studies supporting interventions that directly address stigma among this population are limited [8, 9]. A recent systematic review found that, of the few stigma reduction interventions targeting HIV-positive adolescents in sub-Saharan Africa, intervention duration was between one-half of one day and one week, with longer duration interventions showing stronger effects [10]. The most common interventions provided information and skill-building sessions for HIV-negative individuals [11]. The findings of this review suggested that additional stigma reduction interventions beyond information and skill-building that address a wider variety of stigmas among young people over a longer duration. In a separate review of 48 stigma reduction interventions, only three aimed to reduce stigma among youth living with HIV in sub-Saharan Africa. Most studies were conducted with adults in Asia and the Pacific Region [11]. None targeted HIV-positive children in Northern Uganda. Arts-based intervention studies with young people that are rooted in participants’ ability to control the production and dissemination of knowledge have found reductions in internalized stigma through feelings of empowerment [12–15]. Interventions to reduce stigma need to be culturally grounded and relevant, if they are to change social and cultural norms that reproduce stigma [16]. In general, there is a dearth of evidence-based interventions to address HIV stigma in low- and middle-income countries like Uganda [17], and fewer studies still that have investigated arts-based methods among young people [18]. Given the limited evidence available in support of effective culturally grounded stigma reduction among young people and the push to end the AIDS epidemic by 2030 (Sustainable Development Goals Target 3.3), the identification of effective HIV stigma reduction interventions among this population could have widespread global implications for HIV prevention and care.

The present study will take place in Northern Uganda and will aim to generate much needed evidence for HIV stigma intervention research and practice by developing and evaluating a transformative arts-based intervention involving community members across all stages of the research process [19]. The intervention will be delivered to young people attending school by Elders with the support of teachers through the transfer of local cultural knowledge and practices. Findings will provide insights regarding the use of local cultural knowledge for informing arts-based interventions designed to reduce HIV stigma while improving HIV knowledge, attitudes, and practices among young people. This arts-based intervention will attempt to re-establish the important cultural and social role of Elders within a community that has suffered the loss of intergenerational transfer of cultural knowledge as a result of a 25-year long civil war.

### Objectives

The aim of this study is to design, implement and evaluate an arts-based intervention based on local cultural knowledge to reduce stigma and improve HIV outcomes among young people living with HIV or affected by HIV, aged ≥10 years old. The study is designed to achieve the following objectives:Assess the magnitude of change in measures of stigma (i.e., enacted, internal, anticipated, courtesy, and perceived), HIV knowledge, and fear of transmission and disease among young people who are HIV-positive and HIV-affected and who receive the arts-based intervention;Assess the intervention effect on linkage to care, initiation of ART, adherence to ART, and viral suppression among young people living with HIV;Evaluate how and under what circumstances the intervention had an effect.

## Methods

### Study design

This trial protocol describes a participatory arts-based intervention to be implemented in schools and evaluated using a stepped-wedge cluster randomized trial. This protocol is reported in compliance with the Standard Protocol Items: Recommendations for Intervention Trials (SPIRIT) guidelines (see Fig. 1 and Additional file 1). A formative phase based on qualitative interviews will provide data to inform intervention content and delivery. The intervention will be developed using a series of community-based participatory research (CBPR) meetings with a Community Advisory Committee (CAC) and a group of Elders. A process evaluation occurring throughout the study will evaluate linkages between development, implementation, and intervention effects. The study was designed in partnership with the District Health Officer, the District Education Officer, the AIDS Support Organization (TASO), and the Waroco Kwo Elders Association in Omoro District.

**Fig. 1 Fig1:**
[figure not shown]
SPIRIT flow diagram

The 32-week stepped-wedge cluster-randomized trial will be implemented in three blocks of four schools, each stratified by school type (primary, secondary), such that each block will consist of two schools of each type. The clusters are assembled into three blocks that will crossover from control to intervention condition, with crossover order selected at random. Including the control period, each school will participate across four 8-week periods with crossover from control to intervention condition occurring after each period [20, 21]. Clusters will receive the intervention over 24 weeks, 16 weeks, or 8 weeks depending on their block allocation (Fig. 2).

**Fig. 2 Fig2:**
[figure not shown]
Stepped-wedge design for an evaluation of an arts-based intervention in Omoro, Uganda

### Ethics and informed consent

This study has been approved by the Thompson Rivers University Research Ethics Board (102240) (Additional file 2), the University of Saskatchewan Behavioral Research Ethics Board (Beh-REB1701) (Additional file 3), and the University of Lethbridge Human Participant Research Committee (2020-004) (Additional file 4). In Uganda, the study has been approved by the Uganda National Council for Science and Technology (HS510ES) (Additional file 5) and the AIDS Support Organization (TASOREC/011/2020-UG-REC-009) (Additional file 6).

Information and consent forms (Additional file 7) will be provided to all participants, including students and their guardians/parents, teachers, and Elders. Forms will be drafted in English and translated to Luo. Verbal consent will be obtained prior to participation and recorded. Information and consent forms will inform participants that they may opt-out and withdraw their data at any time throughout the study; however, data cannot be withdrawn once the study has been completed. Participants will also be informed that all data will remain anonymous and confidential and that study results may be shared locally and internationally. This trial does not involve the collection of biological specimens.

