##### Arts-based activities

These activities are anchored in aesthetics, i.e., theory of artful expression [26], and influenced by Eisner’s view that arts-informed research entertains, educates, and acknowledges individuals as knowledge-makers [27]. A key advantage of using art is to access “ways to perceive and interpret the world…that would otherwise go unknown” [27].

During the second hour of the weekly session, the focus will shift to addressing the “problem” through finding “solutions” and encouraging action by learning traditional Ugandan songs and dance; told and acted stories; proverbs and sayings that incorporate empowering messages and moral teachings connected with respect for the relationship between oneself and the community, peers and Elders; and responsibility for others. By grounding the intervention in local culture, this knowledge will reinforce the transformational learning needed to address the root causes of HIV stigma (e.g., stigma toward sex and adolescent sexual and reproductive health) while directly addressing each stigma type (i.e., enacted, internalized, anticipated, courtesy, and perceived). Drawing on the work of Paulo Freire, problem-based identification and discussion occurring in the first hour will be connected with development of problem-solving skills in the second hour [28]. Students will also be invited to write stories and music lyrics or create visual art that draws on their experiences with HIV-related stigma. The audio recordings of weekly sharing sessions will generate data for the process evaluation. Filming of storytelling sessions with Elders during the intervention will serve as knowledge preservation activities that promote intergenerational inclusion.

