##### Participatory theater

After five weeks of intervention activies, a participatory theater intervention (PTI) will occur over the following 3-week period. Developed in collaboration with students, the PTI will summarize learning and cultural traditions from previous sessions. The first week will be dedicated to developing the forum theater event. The remaining two weeks will be dedicated to performances in front of audiences, including students, parents, and community members. Five topical scenes will be developed per school in collaboration with theater specialists, researchers, students, Elders, and teachers. Scenes will be developed through performance techniques [28] that will include a summary of qualitative data findings from formative interviews. Each scene will incorporate examples of stigma types (i.e., enacted, internalized, anticipated, courtesy, and perceived) with an HIV-positive and HIV-affected participant (student actor) who will perform each stigma domain. For example, student actors will portray a student who is living with HIV and experiencing internalized stigma and anticipated stigma; a student not living with HIV who is enacting stigma; a student who is experiencing courtesy stigma because of a mother living with HIV; and a student who perceives stigma in their community. Additionally, after enacted situations that present a problem with no solution, an audience member will be invited to enact a positive solution.

A semi-structured focused discussion will be held immediately after the PTI to explore participant and audience experiences. These discussions will be recorded and transcribed, providing qualitative data for the process evaluation.

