### Data monitoring and adverse events

We have not established a Data Monitoring Committee as the arts-based intervention is considered to be low-risk. Similarly, stopping guidelines and interim analyses were not deemed necessary. Serious adverse events (SAEs) are not anticipated. Minor adverse events (AEs) may occur. For instance, children who live with HIV may be distressed while participating in discussions of stigma and discrimination. Additionally, it is possible that participants may report sexual assault that occurs within the community during the study timeframe, unrelated to study activities. In both cases, initial support will be offered through a trained counselor affiliated with the study. If further assessment or support is needed or the participant does not want to see the counselor, a list of referral agencies will be provided through our research team, who will support the participant to connect with the appropriate agency such as health, legal, livelihood, or security service providers. Any unanticipated SAE will be documented in relation to severity, expectedness, and causality, reported within seven calendar days to Ethics Committees, and discussed at a specially convened TSC meeting. AEs will be documented in the same fashion and discussed at the routine TSC meeting or sooner if an AE is repeated, and may be reported within 14 calendar days to Ethics Committees depending on severity and whether the event was anticipated. Furthermore, participants who report that they are sexually active and engage in condomless sex will be supported to attend the nearest health center for HIV testing and post-exposure prophylaxis as needed within 72 h, or will be provided with TASO’s contact information to receive appropriate counseling and support. Positive tests will be referred for counseling and follow-up per national protocols.

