## Data Availability

Datasets analyzed in this study, statistical codes, and the full study protocol are available from the corresponding author upon reasonable request. Materials will include audio-visual documentation of the arts-based intervention and Elders’ stories, which will be kept on a YouTube Channel that the Waroco Kwo Elders Association administers to promote intergenerational inclusion.

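### The assurance that all data stay anonymous conflicts with the plan's own filming, audio recording, footage sharing and coded-data linkage

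*Protocol article*

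**What the plan says.** All references are to the protocol article.

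- **Ethics and informed consent** summarises what the information and consent forms convey: "Participants will also be informed that all data will remain anonymous and confidential". No exception is made for film, audio or performance. The same section lets participants withdraw their data while the study runs, but adds that "data cannot be withdrawn once the study has been completed".
- **Arts-based activities** says: "Filming of storytelling sessions with Elders during the intervention will serve as knowledge preservation activities that promote intergenerational inclusion". It makes the audio of the weekly sharing sessions a data source for the process evaluation. It also says: "Students will also be invited to write stories and music lyrics or create visual art that draws on their experiences with HIV-related stigma".
- **Participatory theater** has scenes on each type of stigma, "with an HIV-positive and HIV-affected participant (student actor) who will perform each stigma domain", staged before an audience that includes families and other residents. The sentence that follows describes the actors as portraying such students. The discussion after the performance is recorded and transcribed as data.
- **Administrative health data** has a study ID file, linked to identifiers, sent to the partner AIDS service organisation. Records come back under the study ID with identifiers removed.
- **Data Availability** says: "Materials will include audio-visual documentation of the arts-based intervention" and Elders' "stories, which will be kept on a YouTube Channel". The Elders association, not the research team, administers that channel.

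**The concern.** Children from age 10 and their guardians are asked to take part in a trial about HIV stigma. The assurance on anonymity bears directly on what they have most reason to fear. If the plan's own procedures make voices or faces recognisable, and some of that material leaves the research team, then the assurance as written is untrue.

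Being recognised in material about HIV stigma could lead others to guess at a student's or a parent's status, rightly or wrongly. Part of this could be hard to undo. The right to withdraw data ends when the study ends, and the channel is in other hands.

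**Working it through.** No figure in the plan bears on this point, so there is nothing to recompute. The check sets the assurance against each procedure in turn and asks whether both can hold.

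1. **Scope of the assurance.** It covers all data. The audio of the sharing sessions falls within it, because Arts-based activities makes that audio a data source. So do the recorded post-performance discussions.

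2. **Audio.** A recorded voice, speaking among classmates in a session that draws on personal experience of stigma, can be kept confidential. It is not anonymous. The assurance therefore fails for these recordings even if they are never published.

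3. **Film.** The only filming that Arts-based activities describes is of storytelling with Elders. This takes place during the intervention, which is delivered to students in classrooms. The article does not say whether students are in view or audible.

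4. **Sharing.** The Data Availability sentence can be read in two ways.
   - If the clause about the channel covers everything before it, footage of the intervention goes onto the channel.
   - If it covers only the Elders' stories, footage of the intervention is still listed among the materials to be made available.

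   On either reading some intervention footage leaves the research team, and no rule says who may be identifiable in it.

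5. **Coded data.** The linkage in Administrative health data needs a file that ties study IDs to identifiers. Withdrawal during the study also requires that a participant's records can be found. Both describe coded data. The removal of identifiers is described for the linked health records only, not for audio or film.

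6. **Theater.** Taken alone, "with an HIV-positive and HIV-affected participant (student actor) who will perform each stigma domain" can be read as casting by real status. The next sentence has actors portray students living with HIV, and its examples include a student without HIV who stigmatises others. That sentence points to roles. The two should say the same thing, because someone casting from the text could follow the literal words.

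**Result.** The assurance conflicts with the audio recording and with the record linkage as described. It also conflicts with the sharing of intervention footage unless students are kept unidentifiable, and the article does not require that. The theater text is ambiguous rather than contradictory.

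**The case against.** The strongest reply is that a journal article condenses its consent procedures. The forms are in Additional file 7, which is not shown, and they may contain a separate media consent, masking of faces or an opt-out from filming. That stands as far as the actual risk goes: it cannot be said that filming is missing from the forms, or that families agree on a false basis. It does not reconcile the article with itself, because the sentence on anonymity reports what participants will be told and carries no exception.

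A reader might infer more than this. The documents do not support the following.

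- **That all sessions are filmed and students' work is posted publicly.** Filming is described for Elders' storytelling only. The wider reach rests on the broader words in Data Availability. No section says that students' stories, lyrics or art are posted, or that the channel is open to the public. The limit on withdrawal makes later removal uncertain, but it does not show that exposure would be permanent.
- **That students with HIV are put on stage as such.** The portrayal sentence tells against this, and acting a role discloses nothing about the actor.
- **That resulting harm would go unrecorded.** The harms named under Data monitoring and adverse events are examples. The section has adverse events documented for severity, expectedness and causality and discussed by the Trial Steering Committee, with counselling and referral available. A disclosure event that came to the team's notice would fall under that rule.
- **That referral on individual answers breaches confidentiality.** The article says that "participants who report that they are sexually active and engage in condomless sex will be supported to attend" a health center. This shows that answers are traceable to a person, so *anonymous* is the wrong word. A private referral exposes no one to the public.
- **That the trial's effect estimate would be biased, or that a given number of students would be exposed.** Nothing in the article gives a basis for either. Applying the district prevalence of 7.2% to the 900 expected survey completers gives 900 × 0.072 = 64.8. That prevalence is for ages 15–24 while students enter from age 10, and the product counts students living with HIV, not students filmed, cast or recognised.

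**Conclusion.** The concern holds as an inconsistency within the article. The promise that all data are anonymous does not fit the audio recording of sharing sessions, the study-ID linkage, or the sharing of intervention footage without a rule on identifiability. The casting sentence adds an avoidable ambiguity.

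The consequence is that a student could be identifiable in shared footage despite the assurance. Disclosure of HIV status is a step further. It is inferred, and no section states that it will occur.

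The scope is all 12 schools and about 1800 eligible students, because the assurance and the intervention apply to all of them. How many would appear in shared footage cannot be derived from the article. The conclusion rests on two assumptions: that voice recordings count as data, which the article itself says, and that some intervention footage may show or carry the voice of students, which the article neither states nor excludes. A media consent in Additional file 7 would lessen the risk but would leave the text to be corrected.

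**What to change.** 1. **Data Availability.** Limit footage that is shared or placed on the channel to Elders, and to material in which no student can be identified by face, voice or name.
2. **Ethics and informed consent.** Replace *anonymous* with *coded and confidential*. State the exception: some sessions are filmed or audio-recorded, and scenes are performed before an audience. Check that the forms in Additional file 7 say the same.
3. **Participatory theater.** Reword the casting sentence to *a student actor portraying* an HIV-positive or HIV-affected student, and state that roles are assigned without regard to HIV status.
4. **Optional, Data monitoring and adverse events.** Name disclosure of HIV status as an example of an adverse event. The existing documentation rule already covers it, so this only prompts staff to look for it.

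The cost is a few sentences, an editing rule for footage and, if the forms do not already match, a revised information letter. Some student footage could not be published. At version 2.0 of the protocol, study recruitment was still expected to begin, so the wording could be corrected before students were approached.
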